## Abstract

**Simple Summary:**

This is a Phase II randomized controlled trial conducted with the aim of investigating whether the use of Electrochemotherapy after neoadjuvant therapy (ECT) and before surgery in patients with major clinical response allows for a more conservative surgical approach in patients with Locally Advanced Rectal Cancer (LARC) in comparison with the control group that will not receive ECT. The treatment response, in both the control arm and in the treatment arm, will be assessed using the histopathological tumor regression grade on tissue specimens after local excision.

**Abstract:**

Background: Currently, 45–55% of rectal cancer patients receive preoperative chemo- radio-therapy for Locally Advanced Rectal Cancer (LARC). The idea of our study is to use Electrochemotherapy (ECT) before surgery, in patients with major clinical response after neoadjuvant therapy, to allow for a more conservative surgical approach. Objective: To evaluate the increase of the complete response rate after neoadjuvant treatment in LARC and to spare organ function due to total mesorectal excision (TME). Patients and Methods: This is a Phase II randomized controlled trial enrolling 70 patients that will be developed in two stages. In the first step, 28 patients will be enrolled: 14 of these will receive ECT for four weeks after neo-adjuvant treatment and then local excision (treatment group) and 14 patients will receive neo-adjuvant treatment and then local excision (control group). If an increase of response rate is observed in the first stage, and/or feasibility/safety is demonstrated, the second stage of the trial will be performed, enrolling an additional 42 patients. The treatment response. in both the control arm and the treatment arm, will be assessed using the histopathological tumor regression grade on tissue specimens after local excision.

## 1. Introduction

Electroporation (EP) is a technique that is able to increase the permeability of the cell membrane by applying a short and intense electrical field that allows molecules that are not, or barely, permeable, to enter into the cell. Electrochemotherapy (ECT) is the combination of a cytotoxic drug and EP.

After the first electrochemotherapy clinical trials [1,2,3,4], the Standard Operating Procedures for electrochemotherapy with the CLINIPORATOR™ were defined [4,5]. Other studies were carried out that confirmed the clinical effectiveness of ECT and its acceptable safety profile [4,6,7,8,9], as well as that it had significantly higher effectiveness than bleomycin or cisplatin alone [9]. No electrochemotherapy-related serious adverse events were observed [8].

Recently, the feasibility and benefits of ECT have also been observed and documented in deep solid tumors, such as liver metastasis, primitive liver tumors (cholangiocarcinoma and hepatocellular carcinoma) and pancreatic tumors, both in preclinical and clinical studies [10,11,12,13,14,15,16,17,18,19,20,21,22,23,24,25,26], overcoming the difficulty of obtaining the complete electroporation of target lesions. Preliminary results show that the treatment of metastases localized in deep-seated organs is feasible and safe, that ECT is effective in the resolution or regression of tumor nodules, improving patients’ quality of life. Neither acute (intraoperative) nor postoperative serious adverse events, nor clinically significant electrocardiographic, hemodynamic, or serum biologic changes were noted. Amylase or lipase levels were normal in the patients and no bleeding or damage to surrounding viscera occurred [20,21].

Endoluminal allows the endoscopic treatment of colorectal cancer and gastric and esophageal tumors. This device uses a vacuum to capture tumor tissue while an electroporation pulse is applied. Recently, a phase I clinical trial [27] on endoscopic electrochemotherapy for advanced esophageal cancer—the first in humans—has been conducted in six patients using intravenous bleomycin. Treatments were well tolerated, with the main AEs being nausea, vomiting, oral thrush, pneumonia, retrosternal pain, fever, and hoarseness. No serious complications were observed. Five patients had a visual tumor response confirmed by gastroscopy. In two cases, these findings were confirmed with 18F-fluorodeoxyglucose positron emission tomography/magnetic resonance imaging (18F-FDG PET/MRI) as it revealed a reduction of total tumor mass [27].

A phase II clinical trial in non-surgical patients with colorectal cancer is currently ongoing (https://clinicaltrials.gov/ct2/show/NCT03040180, accessed on 10 April 2021). The patients are being treated with bleomycin i.v. according to the ESOPE (European Standard Operating Procedures of Electrochemotherapy) protocol and, in preliminary results, no adverse events or complications have been registered.

Therefore, an endoscopic treatment for colorectal cancer has been investigated and the preliminary results demonstrate that the entire procedure is minimally invasive and completely ambulatory.

## 2. Trial Design

Seventy patients will be enrolled in a Phase II randomized controlled trial. The study will be developed in two stages. In the first step, 28 patients will be enrolled: 14 of these will receive ECT for four weeks after neo-adjuvant treatment and then local excision (treatment group) and 14 patients will receive neo-adjuvant treatment and then local excision (control group). Electrochemotherapy will be performed with the CLINIPORATOR™ and an intravenous dose of Bleomycin. If an increase of response rate is observed in the first stage and/or feasibility/safety is demonstrated, the second stage of the trial will be performed. In the second step, an additional 42 patients will be enrolled and treated. Trial design flow-chart is showed in Figure 1.

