### 2.8. Statistic Considerations

#### 2.8.1. Description of Sample Size Calculation and Planned Statistical Analyses

The sample size was determined by the Group-Sequential Superiority approach with a Margin Tests for the Difference of Two Proportions [36] using a complete response rate to the TRG after local excision as an endpoint. Sample size estimation has been carried out by using the superiority hypothesis in two independent parallel sample proportions [38,39,40,41,42]. According to the literature data, neoadjuvant chemo-radiotherapy treatment in LARC results in a complete response of 25% [43,44,45,46,47,48].

The proportion in the treatment group is assumed to be 0.25 under the null hypothesis and 0.50 under the alternative hypothesis. The proportion in the control group is assumed to be 0.25. The significance level of the one-sided test was targeted at 0.10 and the power at 80%.

An interim analysis will be conducted when 28 patients are enrolled (the percent of the sample size accumulated up to the corresponding look will be 40.0%). If a complete response rate to the TRG after local excision is noted in less than 25% of patients in the treatment group and/or feasibility/safety was not demonstrated, the study will be discontinued, otherwise a further 42 patients will be enrolled in the study.

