#### 2.8.2. Statistical Analysis

The treatment feasibility/safety of surgery following electrochemotherapy will be assessed considering the number of participants with compromised surgery following electrochemotherapy assessed by the R1 resection rate, circumferential resection margin (CRM) involvement, non mesorectal resection plane, and post-operative complications according to the Clavien-Dindo Classification. A surgical complications rate of 30–40% was reported in the literature for conventional neoadjuvant treatment followed by TME [37]. The evaluation of each arm will be performed at Visit 5 (12 weeks from ECT/8 weeks from LE).

Complete response rate (TRG 1 and 2), disease recurrence rates and percentages will be compared among the two groups. A one-sided Fisher exact test will be performed to test the differences between the groups. Differences will be considered significant at *p* < 0.10. A Chi square test will be performed to assess statistically significant differences among the groups for the categorical variable.

The time interval between the recruitment date and local disease progression will be represented using the time of treatment failure and median and minimum–maximum values will be considered.

The scores obtained by the QOL, pain and satisfaction questionnaires will be evaluated. Any serious adverse events and their intensity, according to the NCI-CTCAE classification (version 5.0), will be registered in the first two days post-procedure.

Mean ± standard deviation will be considered for normally distributed continuous variables while the median and interquartile range (IQR) will be presented for non-normally distributed continuous variables.

For continuous variables, the difference between follow-up values and baseline values will be tested by a 2-sided Student t-test or by a Mann–Whitney test while, for the categorical variables, the McNemar test and the marginal homogeneity test will be use [49,50].

Time to event outcomes will be analyzed using the Kaplan–Meier method and survival curves will be compared using the log-rank test.

Mixed effect regression models will be used to analyze longitudinal data by adjusting for proper covariates.

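### The rule for opening stage 2 is stated in two incompatible forms: the abstract and Section 2 continue if one condition is met, while Sections 2.8.1 and 2.8.3 stop if one condition fails

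*Protocol article*

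**What the plan says.** The decision after the first 28 patients is described in four places of the protocol article.

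- **Abstract:** "If an increase of response rate is observed in the first stage, and/or feasibility/safety is demonstrated, the second stage of the trial will be performed".
- **Section 2 (Trial Design):** the same sentence, "If an increase of response rate is observed in the first stage and/or feasibility/safety is demonstrated, the second stage of the trial" goes ahead. No threshold is given and no comparator is named for the increase.
- **Section 2.8.1:** the trigger for stopping is complete response by TRG observed in "less than 25% of patients in the treatment group and/or feasibility/safety was not demonstrated, the study will be discontinued". If neither failure occurs, 42 more patients join the trial.
- **Section 2.8.3 (Interim Analysis):** the same stopping rule as 2.8.1. It adds that a 20% difference between arms in the AE rate and the surgical complications rate is enough to discontinue.

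On timing, Section 2.8.1 says "An interim analysis will be conducted when 28 patients are enrolled", whereas Section 2.8.3 places the analysis after the first step of the study. TRG is read at Visit 4 (Day 37, Table 2). For surgical feasibility and safety, Section 2.8.2 says "The evaluation of each arm will be performed at Visit 5 (12 weeks from ECT/8 weeks from LE").

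**The concern.** A rule to continue and a rule to stop must be complements: every possible interim result should lead to exactly one action. Here both rules join their conditions with the same inclusive connector. The complement of stopping when either condition fails is continuing only when both hold, and that is not what the abstract and Section 2 say.

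This is the trial's single go/no-go decision. It governs the enrolment of 42 further patients and includes the safety condition, and feasibility/safety is the first primary endpoint in Section 2.1.1. If one condition passes and the other fails, either action can be defended by citing the protocol after the data have been seen.

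**Working it through.** **Inputs.** Total 70, with 28 in stage 1 and 14 per arm (Section 2). Control 25%; ECT 25% under the null and 50% under the alternative; one-sided 0.10, power 80% (2.8.1). Enrolment over 36 months (2.4).

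**The plan's own figures.** 28/70 = 40.0%, as stated. For a fixed design with p̄ = 0.375, n per arm = [1.2816·√(2·0.375·0.625) + 0.8416·√(0.25·0.75 + 0.5·0.5)]² / 0.25² = 32.9, so 33 per arm and 66 in all. Allowing for one look at 40% gives 64 to 74 in total, depending on the spending function (O'Brien-Fleming or Pocock type) and the variance form. Seventy lies inside that range, and the normal-approximation power at 35 per arm is 0.818. The sample size is not in question here.

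**The logic.** Suppose first that both texts used the same response criterion, and read the connector as written (either or both):

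| Response condition | Safety condition | Abstract, Section 2 | Sections 2.8.1, 2.8.3 |
|---|---|---|---|
| met | met | continue | continue |
| met | not met | continue | stop |
| not met | met | continue | stop |
| not met | not met | not opened | stop |

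The texts agree only in the first and last rows. Reading the connector as a strict *and* everywhere does not help. With exactly one failure, Section 2 would not open stage 2, while 2.8.1 would enrol the further 42.

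**How often, with safety shown.** Section 2 continues whatever the response. Section 2.8 stops when fewer than 25% of 14 respond; 0.25 × 14 = 3.5, so at 3 or fewer.

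P(X ≤ 3) = Σ(k = 0 to 3) C(14,k) p^k (1−p)^(14−k)

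- p = 0.25: 0.0178 + 0.0832 + 0.1802 + 0.2402 = 0.521
- p = 0.375: 0.168
- p = 0.50: (1 + 14 + 91 + 364)/16384 = 470/16384 = 0.029

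These figures do not depend on what *increase* means.

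**How often, with safety not shown.** Section 2.8 stops. Section 2 continues if there is an increase, so the figure depends on the comparator:

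- *Increase* read as more ECT than control responders, control at 25%: conflict in 41% of trials at a true ECT rate of 25% and 89% at 50%.
- *Increase* read as above the fixed 25%: 1 − 0.521 = 48% and 1 − 0.029 = 97%.

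**The two response criteria.** Under the versus-control reading only, 3/14 against 1/14 is an increase yet below 25%, and 4/14 against 5/14 is at least 25% yet no increase. At 25% in both arms these two kinds of disagreement have probabilities 8.7% and 15.3%, 24% together. If *increase* means above 25%, the disagreement vanishes.

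**Timing.** Visit 1 may precede Day 0 by up to a month. TRG therefore comes about 37–67 days after enrolment and Visit 5 about 84–114 days (2.8 to 3.7 months). Assuming uniform accrual of 70/36 = 1.94 per month, a look on the very day of the 28th enrolment would lack TRG for about 2–4 patients and Visit 5 data for about 5–7.

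**The case against.** The strongest reply is that the operative rule is in the statistical sections. Sections 2.8.1 and 2.8.3 agree with each other and give a numeric response limit; 2.8.1 adds an explicit *otherwise* branch and 2.8.3 a safety margin. The abstract and Section 2 are one-sentence overviews, and their connector also admits *and*, which would match 2.8. This has weight: most statisticians would follow 2.8. But it requires reading the same connector as *and* in one place and *or* in the other, and nothing in the article says which text prevails.

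Three stronger readings are tempting and are not supported.

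- **That the plan lets an unsafe but active ECT proceed.** This follows only if the overview sentence overrides two explicit stopping statements. The probabilities above also condition on safety being shown or not, and the article gives no probability for either. They measure how often the texts differ, not how often a wrong decision would follow.
- **That Section 2 prescribes a comparison with the control arm.** It names no comparator. The Discussion does speak of an increase relative to control, but as the trial's outcome, not the interim criterion. The 24%, 41% and 89% figures are therefore conditional on that reading.
- **That the decision will be taken on incomplete outcomes.** Section 2.8.3 puts the look after the first step, Section 2 describes that step as running through local excision, and the criterion is TRG noted after excision. The figure of 28 enrolled may simply fix the size of the look. An immature look is possible but not shown. Nor does the article say that pending patients would count as non-responders. With 12 of 14 ECT results in hand and 12 as denominator, stopping needs at most 2 responders: P = 79/4096 = 1.9% at a true 50%, below the 2.9% with full data.

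**Conclusion.** The contradiction is real and lies in the text. It does not rest on the sample size, and no single reading of the connector removes it. Its firm size is the case with safety shown: 52% of trials at a true ECT rate of 25% and 2.9% at 50% would meet both the rule to continue and the rule to stop. This assumes 14 evaluable ECT patients, independent responses and the literal inclusive reading. The different wording of the response condition is a second mismatch, so aligning the connector alone would not fully reconcile the texts. The timing wording is unclear rather than wrong. The point should be settled before the interim; which criterion is right is for the sponsor.

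**What to change.** Before the interim, reconcile the abstract and Sections 2, 2.8.1 and 2.8.3 into one go/no-go rule, stated identically in all four places. The continue rule should be the exact logical complement of the stop rule, with a single response criterion. The sponsor chooses the criterion.

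If a comparison with the concurrent control is considered, its operating characteristics must be reported, because it is a design change and not a rewording. Requiring more ECT than control responders at 14 per arm stops 1 − 0.887 = 11.3% of trials at 25% versus 50%, against 2.9% under the fixed 25% limit. Power of the planned one-sided Fisher test at 35 per arm, counting early stops as failures, falls from 72.8% to 70.5%.

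Align the trigger in 2.8.1 with that in 2.8.3, so that it is clear the look uses TRG and Visit 5 surgical-safety data from all 28 patients.

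The cost is protocol wording and an interim about 3–4 months after the 28th enrolment.

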### 2.1. Objectives

#### 2.1.1. Primary Endpoints

1. To assess electrochemotherapy feasibility/safety.

2. To evaluate the complete response rate increase with the aim of organ sparing.

3. Histopathological analysis evaluation will be based on the tumor regression grade (TRG) by Mandard et al. [28], performed on tissue specimens by local excision.

#### 2.1.2. Secondary Endpoints

To evaluate the local recurrence rate, pain control, quality of life and electrochemotherapy toxicity.

### 2.2. Subject Selection

Eligible patients will be randomly assigned (1:1) to the treatment group or the control group. The treatment group assignment will be assigned blindly and sequentially in the order in which eligible patients are enrolled in the study. Patients eligible for inclusion in the protocol (see Table 1) will be informed in detail about the study and, if they consent to participate, they will sign the informed consent form (Appendix A), witnessed by a member of the research group.

### 2.3. Subjects Treatment

Both the Control group and the Treatment group will receive neoadjuvant treatment, either long course radiotherapy with concomitant chemotherapy or short course radiotherapy, before local excision (LE). Long course radiotherapy consists of 45–50 Gy (in fractions of 1.8–2 Gy), with concurrent 5-fluorouracil. Standard fractions of 1.8 Gy/day to the reference point will be given five times a week up to a total dose of 50.4 Gy in 28 fractions [29]. Each subject will receive the standard treatment with capecitabine at a dose of 825 mg/m^2^ twice daily, five days a week, for five weeks.

Short course radiotherapy consists of a dose of 25 Gy in five fractions over one week [29].

External radiation therapy will be performed using a 3-field (one posterior–anterior and two lateral fields) or IMRT (Intensity Modulated Radiation Therapy) technique.

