### 2.5. Description of Study Procedures

Quality of life (QoL), as measured by the EQ5d questionnaire, will be completed at Visits 1, 2, 3, 5, 6, 7, 8, 9, 10, 11 and 12 and will be considered optional from visit 13 to 18. The EQ-5D was developed in Europe and it is a descriptive system of preference-based Health Related Quality Life [30]. The EQ-5D questionnaire also includes a VAS, by which respondents can report their perceived health status with a grade ranging from 0 (the worst possible health status) to 100 (the best possible health status). Pain will be assessed at Visits 1, 2, 3, 5, 6, 7, 8, 9, 10, 11 and 12.

#### 2.5.1. Visit 1

All patients will undergo the same enrollment/baseline visit (Visit 1) procedures. Clinical examination will include the measurement of weight, height and vital signs (pulse, blood pressure). Patients must sign the informed consent form. The Screening/Enrollment Visit (Visit 1) procedures must be performed not more than 12 (±1) weeks after the end of neoadjuvant therapy. Patients who fulfill all inclusion criteria will be enrolled. Patients who are Eastern Cooperative Oncology Group ECOG (ECOG) Performance Status grade 0, 1 or 2 are eligible for study participation [31].

Study procedures at Visit 1 consist of the following: screening against inclusion/exclusion; randomization to ECT or standard treatment; and Complete Blood Count (CBC) and coagulation profiles evaluation. An absolute neutrophil count below 1000/mL, a platelet count below 70,000/mL, and/or an international normalized ratio (INR) above 1.5 will be considered exclusion criteria. The patients will be subjected to rectal exploration; rectoscopy; routine hematochemistry and carcinoembryonic antigen (CEA), Magnetic Resonance (MR) with contrast medium (cm) and Computed Tomography (CT) with contrast medium. Medical and Oncology history, including any previous treatments, concomitant treatments, medications, and events will be registered. Pain will be evaluated according to the Visual Analog Scale (VAS) scale and Quality of Life will be monitored according to the EQ5d questionnaire.

All patients will undergo a pre-anesthetic visit and will be excluded from study participation if not eligible for general anesthesia or monitored anesthesia care (conscious sedation).

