The idea is to use electrochemotherapy in patients with LARC and major clinical response after neoadjuvant therapy, before surgery (local excision of the rectum as the surgical approach used in clinical practice) and assuming an increase in the local control of residual disease and of complete response rate, confirmed by histopathological examination using Tumor Regression Grade. The TRG is a powerful indicator of response to a neoadjuvant treatment in rectal cancer and can measure the effectiveness of neoadjuvant therapy.

ECT has been shown to have limited side effects, a high degree of patient acceptability and acceptable costs. Treatment is performed under local or general anesthesia and does not always require hospitalization. The outcome is to verify the feasibility/safety of electrochemotherapy in this indication and the increase of complete response rate in the treatment group with respect to control group.

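### The TRG 1–2 comparison is fixed as an unadjusted test although neoadjuvant regimen is known before randomisation: a weakness in precision and conditional interpretation, not a type I error flaw

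*Protocol article*

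**What the plan says.** All references are to the protocol article.

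- **Background treatment (2.3).** Both arms receive "either long course radiotherapy with concomitant chemotherapy or short course radiotherapy, before local excision (LE". Long course is given up to 50.4 Gy in 28 fractions with concurrent chemotherapy. Short course is 25 Gy in five fractions, and no concurrent chemotherapy is described for it.
- **Allocation (2.2).** "Eligible patients will be randomly assigned (1:1) to the treatment group or the control group". The next sentence adds: "The treatment group assignment will be assigned blindly and sequentially in the order in which eligible patients are enrolled in the study". A balancing factor is neither named nor excluded.
- **Timing (2.5, Visit 1).** The Visit 1 procedures include "randomization to ECT or standard treatment". Visit 1 takes place at restaging, after neoadjuvant therapy has ended, and previous treatments are recorded there.
- **Primary comparison (2.8.2).** For TRG 1 and 2: "A one-sided Fisher exact test will be performed to test the differences between the groups", at p < 0.10. Covariate adjustment is mentioned only for longitudinal data.
- **Endpoint (3, Discussion).** "The TRG is a powerful indicator of response to a neoadjuvant treatment in rectal cancer and can measure the effectiveness of neoadjuvant therapy".
- **Planning rate (2.8.1).** A single control rate of 25% is used, with literature support cited for chemo-radiotherapy.
- **Size (2 and 2.8.1).** "Seventy patients will be enrolled in a Phase II randomized controlled trial", hence 35 per arm. "An interim analysis will be conducted when 28 patients are enrolled", hence 14 per arm.

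**The concern.** On the article's own description, TRG reflects how well the neoadjuvant therapy worked. The regimen may therefore act directly on the endpoint by which ECT is judged. It is a binary baseline fact, settled before allocation and already recorded, yet the one efficacy test fixed in print does not use it.

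With 35 patients per arm, simple 1:1 allocation can leave the arms noticeably different in regimen mix. If the regimens differ in TRG response, the crude difference then contains part of the regimen effect. Only one trial will be run. After an unlucky split, its readers could not tell from the planned test how much of the difference belongs to ECT.

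**Working it through.** **1. The plan's sample size.** Inputs from 2.8.1: 0.25 v 0.50, one-sided alpha 0.10, power 80%, one look at 40%. The fixed design needs, per arm,

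n = [z(0.90)·√(2·0.375·0.625) + z(0.80)·√(0.25·0.75 + 0.50·0.50)]² / 0.25² = [1.2816·0.6847 + 0.8416·0.6614]² / 0.0625 = 32.9,

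which is 33 per arm or 66 in total. Inflated for two looks, the total is 68 with O'Brien-Fleming-type spending and 72 with linear spending. The stated 70 is thus reproduced within 2; the boundary type is not given. At 35 per arm the normal approximation gives 81.8% power. The Fisher test itself gives 73.8% by exact enumeration.

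**2. How uneven the arms can be.** Assumption, not in the documents: 50% (or 30%) of patients have short course. The difference in short-course share between arms has SD √(2·0.5·0.5/35) = 0.12, or 12 points. A gap of 7 patients is 7/35 = 20 points. The chance of 7 or more extra short-course patients in the control arm is 6.0% with 50% short course and 4.5% with 30%. If exactly 35 of the 70 have short course, it is 7.5%.

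**3. Size of the shift.** Shift in the response difference = difference in share × regimen gap. For a 20-point difference in share this is 0.20 × 10 = 2 points or 0.20 × 20 = 4 points. The target effect is 25 points, and the null standard error is √(2·0.25·0.75/35) = 0.1035.

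**4. Fisher averaged over all splits.** Under simple randomisation each patient in either arm is drawn from the same regimen mixture. With an overall null rate of 25%, the responders in each arm follow Binomial(35, 0.25), whatever the regimen gap. The one-sided Fisher test at p < 0.10 then rejects 6.4% of the time, whether the gap is 0, 10 or 20 points.

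**5. Fisher given an uneven split, and the stratified alternative.** Assumption: long course responds better by the stated gap. If the reverse held, the directions would swap. Fisher figures are by exact enumeration. Stratified exact figures are by simulation, with regimen as stratum.

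| Short course | Gap | Fisher null rejection, ≥7 extra short course in control | Same, ≥7 extra in ECT arm | Stratified exact, ≥7 extra in control | Overall power: Fisher / stratified exact |
|---|---|---|---|---|---|
| 50% | 10 points | 9.6% | 3.9% | about 6% | 74% / 74% |
| 50% | 20 points | 13.8% | 2.1% | about 6% | 74% / 76% |
| 30% | 10 points | 9.6% | 3.9% | about 6% | 74% / 74% |
| 30% | 20 points | 13.6% | 2.2% | about 6% | 74% / 75% |

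Uneven splits also cost power when they run against ECT. With 21 short-course patients in the ECT arm and 13 in control, Fisher power for 0.25 v 0.50 falls to 67% (10-point gap) or 59% (20-point gap).

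**6. Mantel-Haenszel version.** With 50% long course, the regimen-stratified test without continuity correction rejects a true null about 10% of the time whatever the split, with power of 81.6% (10-point gap) or 82.8% (20-point gap). With the correction it rejects about 6%, with power of 74.1% or 75.3%. Most of the gain in the uncorrected version comes from using the full nominal level, not from the stratification.

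**The case against.** The strongest reply is that the planned test is valid. Randomisation makes regimen imbalance part of the chance variation that Fisher's test already allows for, and the overall false-positive rate is 6.4%, well under 10%. That stands. A reader might infer an inflated type I error or a biased trial, and the documents do not support either.

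The decisive input is also assumed. The article gives no response rate by regimen and no expected mix. Only patients with a confirmed major clinical response enter (Table 1), so a difference between regimens in unselected patients need not persist here. At a 10-point gap, even the uneven splits in the table stay just under 10% with Fisher. This too stands, and it limits the size of the point.

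A reader might extend the point to the interim analysis and say that imbalance at 14 v 14 could pass for an ECT effect. The operative response rule in 2.8.1 and 2.8.3 is a 25% threshold on the ECT arm alone, so a difference between arms plays no part in it. The regimen mix within that arm can move the decision to continue: under the null, with a 20-point gap, the chance of continuing is 38% with 5 of 14 on long course and 58% with 9 of 14. That is a separate matter.

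A reader might also conclude that randomisation is unstratified. The article does not say so. It condenses a fuller protocol, and its silence on balancing factors is not evidence. This reply does not reach the primary test, which the article states outright.

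**Conclusion.** The point holds as one of precision and conditional interpretation. The plan pools two regimens and fixes a crude test of an endpoint that it ties to neoadjuvant effectiveness, while leaving unused a baseline factor it already records. Overall false-positive risk is not affected.

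The consequence is confined to unfavourable splits, about 4–6% of trials in ECT's favour. There the null rejection rises from 6.4% to about 10% (10-point gap) or 14% (20-point gap), while the stratified exact test remains near 6%. Splits of the same size against ECT reduce power. These figures assume 30–50% short course, an overall null response of 25%, and a regimen gap of 10–20 points, none of which the documents give by regimen. With no gap the problem disappears, and the stratified exact test has about the same overall power as Fisher (74%).

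The change is worth making because it is cheap and has essentially no downside, not because the present test is invalid.

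**What to change.** In 2.8.2, replace the crude Fisher test of TRG 1–2 with a one-sided test at 0.10 stratified by neoadjuvant regimen (long v short course), and report the regimen-adjusted risk difference with it. The test may be exact or Mantel-Haenszel. The choice, including any continuity correction, should be stated in advance, since it decides whether the test runs near 6% or near 10%.

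If the full protocol does not already do so and enrolment has not started, regimen should also be the stratification factor in the 1:1 randomisation. If enrolment has begun, the analysis change alone is enough, provided it is made before outcomes are seen by arm.

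The cost is one sentence in 2.8.2 and, where still possible, one binary factor in the randomisation list. No patients or assessments are added, because previous treatment is already recorded at Visit 1. The small downside is that a stratum with very few patients would add little information.
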